### Criteria for discontinuing or modifying allocated interventions

Each participant has the right to withdraw from the trial at any time. Participants may discontinue trial participation at any time and are requested to contact a research team member to inform them of their decision. In addition, the Investigator may discontinue a participant from the trial at any time if the investigator considers it necessary for any reason including:

Pregnancy.Ineligibility.Significant protocol deviation.Significant non-compliance with the protocol.Disease progression which results in inability to continue with the protocol.Withdrawal of consent.Loss to follow-up.Significant elevated risk due to hyperkalemia.

Withdrawal will not result in exclusion of the data for that participant from analysis. As the primary analysis will be based on an intention-to-treat there will also be a completer only analysis performed. If the participant is withdrawn within the first two weeks of the trial they will be replaced. If the replacement participant is withdrawn there will be no subsequent replacement. The reason for withdrawal will be recorded in the case report form (CRF), if provided.

### Strategies to improve adherence to interventions

Participants enrolled in both intervention groups will be provided with weekly home delivery of fruit and vegetables to be used in the intervention. There will also be weekly check-ins via email or phone calls to participants regarding the weekly delivery of the fruit and vegetables where coordinators will make sure the delivery contents are acceptable to the participant, with modifications to the delivery contents made according to participant feedback in order to enhance adherence.

### Relevant concomitant care permitted or prohibited during the trial

All participants enrolled in the study will continue to receive multidisciplinary CKD care during and after the trial. Patients that are already on potassium binding therapy will be excluded from this trial. If it is determined that a participant needs to start potassium binding therapy they will be withdrawn from the trial and the reason for withdrawal will be recorded.

### Outcomes

The primary outcome is evaluating sK concentration during the five timepoints at week 0, 1–2, 8, 10 and 16. The secondary outcomes include assessing health related quality of life through KDQOL-SF and STS5 which will be assessed throughout the trial, analyzing clinical chemistry systolic and diastolic blood pressure, and assessing dietary data using the information received from ASA24. Clinical chemistry will look at sodium, potassium, urea, phosphate, and the albumin/creatinine ratio in the urine alongside the collection of blood samples for serum potassium, hemoglobin A1C, albumin, bicarbonate, calcium, chloride, creatinine, eGFR, glucose, phosphorus, sodium and blood urea nitrogen measurement. All samples will be collected and processed by the Diagnostic Services of Manitoba. Individuals will be scheduled for an in-person visit which will include a clinical exam and blood sample to monitor serium potassium and bicarbonate during weeks 1 or 2. Secondary outcome measures will be measured on week 0, 8, 10 and 16. Additionally, anthropometric measurements such as height, weight and BMI will be collected at baseline alongside blood pressure in triplicate.

### Participant timeline

See Appendix A.

For the first two weeks, all participants will start on a liberalized potassium run-in period. Following the run-in period, the participants will be randomized to either the experimental group or the standard care group for six weeks. After the six weeks, a crossover will occur after a two-week washout period.

### Sample size

It has been estimated that a sample size of thirty individuals with each sex will provide 80% power to detect a minimal clinically important difference of 0.35mmEq/L, the reduction shown with a starting dose of Patiromer (4.2 g twice daily) in a double-blind placebo-controlled trial of patients with CKD and hyperkalemia [14]. This assumes a within-subject standard deviation of 0.46, based on a 95% confidence interval of (0.38, 0.72) mEq/L seen in a similar 29-participant cross-over study unpublished, summary results of NCT00949585 found in appendix of Marklund et al [15].

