**Discussion:**

30 male and female CKD outpatients, ≥ 18 years of age, who have an estimated glomerular filtration rate (eGFR) between 15 and 45 ml/min/1.73m^2^ and serum K between 4.5 and 5.5 mEq/L. This design would have greater than 80% power to detect a difference of 0.35 mEq/L serum K between groups. Anthropometric measurements, clinical chemistry, dietary recalls, physical function assessments, as well as a quality of life assessments will also be measured in this trial. These findings will provide high quality evidence for, or against, recommendations for dietary K restriction in individuals living with CKD. The removal of K restriction could provide individuals living with CKD more dietary choice leading to improved dietary status and quality of life.

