### Trial design

This study is an open-label, randomized 2-period crossover definitive superiority trial. The study will be sixteen weeks in duration. Thirty male and female individuals living with CKD will be recruited, with a minimum 40% of each sex. Participants will be randomized to receive both restricted (standard care) and liberalized (experimental) K content fruit and vegetables for six weeks.

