### Recruitment

The recruitment for this study will be done by the research coordinator who will work directly with a healthcare professional (such as a nurse or physician) within the participants circle of care. The healthcare professional will help identify potentially eligible participants. If the participant consents to be contacted, the research coordinator will meet the participant through a virtual meeting or an in-person visit to collect informed consent to participate in the study. A total of thirty participants will be recruited to participate in this study, from Seven Oaks Hospital and Health Sciences Centre renal clinics in Winnipeg, Manitoba. The recruitment period is targeted to last thirty weeks, with enrolment predicted to go at a rate of one participant per week.

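### The SD of 0.46 is labelled within-subject, but the interval cited for it most plausibly gives 0.46 as the SD of paired differences, so it is unclear what the stated 80% power refers to

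*Protocol article*

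**What the plan says.** All locations are in the protocol article.

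- **Sample size** takes a "minimal clinically important difference of 0.35mmEq/L" and assumes a "within-subject standard deviation of 0.46, based on a 95% confidence interval of (0.38, 0.72) mEq/L seen in a similar 29-participant cross-over study". The source is described as unpublished, with summary results in the appendix of another paper. The section does not say which quantity the interval estimates.
- The same section states that "a sample size of thirty individuals with each sex will provide 80% power".
- **Trial design** says "Thirty male and female individuals living with CKD will be recruited, with a minimum 40% of each sex", and **Recruitment** says "A total of thirty participants will be recruited to participate in this study".
- The **Abstract** (Discussion paragraph) says "This design would have greater than 80% power to detect a difference of 0.35 mEq/L serum K between groups".
- **Statistical methods** describes the primary analysis as in essence a paired comparison of the two period endpoints, with sex as a fixed factor. It uses a 0.05 threshold without stating sidedness.

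**The concern.** In a two-period crossover the within-subject SD (the SD of one measurement about the person's own mean) and the SD of the paired differences are not the same. The second is √2 times the first. Swapping one for the other doubles or halves the variance that enters the power calculation.

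The interval offered as the source appears to give 0.46 as the second quantity, while the text names the first. This is the trial's only sample-size justification, so the label decides what a reader takes the trial to be able to detect. It also decides how much loss of participants the design can absorb. The wording on sex adds to the doubt, because it leaves open whether 80% describes all thirty participants or each sex separately.

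**Working it through.** **Inputs.** Difference 0.35 mEq/L, SD 0.46, and a 95% interval of 0.38 to 0.72 from 29 crossover participants (Sample size); 30 participants in total (Trial design, Recruitment); threshold 0.05 (Statistical methods), taken as two-sided by assumption. Power is from the non-central t distribution with n − 2 degrees of freedom unless stated, with non-centrality 0.35 / (SD of differences / √n).

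**1. The plan's own figure, with the label as printed.**
- SD of differences = √2 × 0.46 = 0.651.
- Non-centrality at n = 30: 0.35 / (0.651/√30) = 0.35 / 0.1188 = 2.95.
- Power = 81.2% (normal approximation 83.8%). The smallest n reaching 80% is 30.

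The stated 80% therefore follows if 0.46 really is a within-subject SD.

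**2. What the cited interval gives.** Half-width = (0.72 − 0.38)/2 = 0.17. Read as the interval for a mean paired difference, the SD of differences is half-width / critical value × √n:

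| Calculation | SD of differences | Within-subject SD (÷ √2) |
|---|---|---|
| 0.17/1.960 × √29 | 0.467 | 0.330 |
| 0.17/1.960 × √28 | 0.459 | 0.325 |
| 0.17/2.048 × √29 (t, df 28) | 0.447 | 0.316 |

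So 0.46 falls in the column for the SD of differences. Rounding of the interval limits does not change this: limits of 0.375 and 0.725 give 0.481 (z) or 0.460 (t), and limits of 0.385 and 0.715 give 0.453 or 0.434.

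**3. Other readings of the interval.**
- If 0.46 were the within-subject SD of the source study, its interval would have half-width 1.960 × 0.651/√29 = 0.237 (z) or 2.048 × 0.651/√29 = 0.247 (t), not 0.17.
- If the interval were for an SD of 0.46 itself, the chi-square limits with df 28 would be 0.365 and 0.622. Their ratio is 1.70 whatever the SD, against 0.72/0.38 = 1.89.

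Neither fits.

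**4. Power for 0.35 with 0.46 as the SD of differences.**

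| Participants analysed | Power (t) | Power (normal) |
|---|---|---|
| 30, both sexes | 98.0% | 98.6% |
| 24 completers (assumed number) | 94.5% | 96.1% |
| 15, one sex | 77.8% (78.2% with df 14) | 83.8% |
| 12, one sex at the 40% minimum | 66.2% | 75.0% |

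At n = 30, SDs of 0.447 and 0.467 give 98.5% and 97.7%. Power of 80% for 0.35 needs 16 participants. With all 30, the difference detectable with 80% power is about 0.245 mEq/L.

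**5. Can the stated 80% show how it was obtained?** No. The standard error is the same in two cases: 0.651/√30 = 0.1188 (0.46 as within-subject SD, all thirty) and 0.46/√15 = 0.1188 (0.46 as SD of differences, fifteen of one sex). The normal approximation gives 83.8% for both, and the t results are 81.2% and 77.8%.

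**The case against.** The protocol does not say what the interval is for, and its source cannot be checked from the document. The paired-difference reading is therefore an inference, and that limit stands. It is still the only reading tried here that returns 0.46.

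The label may be loose usage, with within-subject SD meaning the SD of within-subject differences. In that case 0.46 agrees with its source. The wording would still need correcting, because a reader who takes it at face value gets 81% rather than 98%.

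The strongest objection concerns the 80%. A reader might infer that √2 was applied twice and that the stated power is simply wrong. The document does not support that. The sentence on sex can be read as power within each sex, and 15 per sex with 0.46 as the SD of differences gives about 78% to 84%. The minimum share of each sex, the stratification by sex and the sex term in the model are compatible with that reading but do not prove it. Against it, no within-sex analysis is described, and a sex at the 40% minimum would have only about 66%. The origin of the 80% remains open.

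A reader might also take the same phrase to mean thirty of each sex, or sixty in all. Trial design and Recruitment both fix thirty in total, so the phrase needs clarifying and is no evidence of a different sample size.

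**Conclusion.** The point holds as a labelling error with an unclear power statement, of moderate severity. If the cited interval is for a mean paired difference, 0.46 is the SD of paired differences, and the within-subject SD is about 0.32 to 0.33. Overall power for 0.35 mEq/L at n = 30 is then about 98% (two-sided 5%), not 80%. The 80% is right only if 0.46 is truly within-subject, which the interval does not support, or approximately right if it means power within one sex.

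Two stronger conclusions do not follow:

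- **The trial is not shown to be underpowered or fragile.** The error is conservative for the whole sample. As labelled, power does slip to 79.8% with 29 participants, but that uses the SD that the interval does not support. On the supported SD, an assumed 24 completers still give 94.5%.
- **The Abstract is not wrong.** Its claim of more than 80% power agrees with both 81% and 98%.

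**What to change.** Revise the Sample size section as follows:

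1. Confirm what the cited interval estimates. If it is a mean paired difference, relabel 0.46 as the SD of within-person differences and give the within-subject SD as about 0.33.
2. State whether the 80% refers to all thirty participants or to each sex separately. Reword the phrase on sex to match, rather than simply deleting it, and keep thirty in total as in Trial design and Recruitment.
3. Restate the power. Possible wording: *Thirty participants in total, both sexes combined, give about 98% power to detect 0.35 mEq/L (two-sided 5%), or 80% power to detect about 0.245 mEq/L, with an SD of within-person differences of 0.46.* If within-sex power is intended, add about 78% at 15 per sex, and about 66% if one sex has only 12.
4. If 0.46 is kept as a deliberately conservative within-subject SD, say so and drop the claim that it derives from the interval. The 81% then stands as an assumption.

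The Abstract needs no change. The cost is a text correction, with no change to sample size, design or analysis.

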### Objectives

The objectives of this trial are to evaluate the impact and safety of dK liberalization with fruit and vegetables on sK concentrations and to monitor the effects it may have on their physical function and overall quality of life in patients with CKD.

For this trial, our primary hypothesis is that liberalization of dietary K intake, via the provision of higher K fruit and vegetables will be non-inferior to the standard recommended CKD diet in terms of change in sK concentrations. We also hypothesize that liberalization of dietary K will improve self-reported quality of life and lower blood pressure.

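### The 80% power is for detecting a 0.35 mEq/L difference, not for the non-inferiority hypothesis named as primary, which has no stated margin or assumed true difference

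*Protocol article*

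**What the plan says.** Three sections of the protocol article bear on what the trial sets out to show.

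- Objectives: the primary hypothesis is that liberalization "will be non-inferior to the standard recommended CKD diet in terms of change in sK concentrations".
- Trial design: the study is an "open-label, randomized 2-period crossover definitive superiority trial".
- Sample size: "a sample size of thirty individuals with each sex will provide 80% power" and this power is "to detect a minimal clinically important difference of 0.35mmEq/L". The 0.35 is taken from a placebo-controlled trial of a potassium binder. The SD of 0.46, described as within-subject, comes from another study and is "based on a 95% confidence interval of (0.38, 0.72) mEq/L seen in a similar 29-participant cross-over study".

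Recruitment fixes the total: "A total of thirty participants will be recruited to participate in this study". Statistical methods describes a mixed model that amounts to a paired comparison of the period endpoints, with significance at p below 0.05. The article gives no non-inferiority margin and no true difference assumed under the hypothesis. It does not say in words what the interval (0.38, 0.72) estimates.

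**The concern.** Power to detect a difference and power to show non-inferiority answer different questions. The first rises as the true difference moves away from zero; the second falls as the true difference approaches the margin. They coincide at 0.35 only when non-inferiority power is evaluated at a true difference of exactly zero. The stated 80% therefore does not tell the reader how likely the trial is to support its primary hypothesis.

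The interval used for the SD makes this more than a labelling matter. If it describes a mean difference in serum potassium between diets, it lies entirely above the only threshold in the document, and the article does not comment on that. If the conflict were settled simply by relabelling the trial as non-inferiority, the power figure would remain uninformative, and a failure to show non-inferiority could reflect the planning and not only the diet.

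**Working it through.** **Inputs.** N = 30 in total (Recruitment); difference 0.35 mEq/L, SD 0.46, source interval (0.38, 0.72) and source n = 29 (Sample size); p below 0.05 (Statistical methods). Sidedness is not stated, so I assume two-sided 0.05 for a test of difference and one-sided 0.025 for non-inferiority.

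**1. Reproduce the stated 80%.** With 0.46 as the within-subject SD, the SD of paired differences is √2 × 0.46 = 0.651 and the standard error is 0.651/√30 = 0.119. Noncentrality is 0.35/0.119 = 2.95. The noncentral t on 28 df gives 81.2%, and the smallest N reaching 80% is 30. The stated figure is reproduced as power for a test of difference. If 0.46 is instead the SD of the differences, the power is 98.0%.

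**2. What the cited interval is.** Half-width (0.72 − 0.38)/2 = 0.17; midpoint (0.38 + 0.72)/2 = 0.55.

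- As an interval for a mean paired difference with n = 29, the SD of differences is 0.17/2.048 × √29 = 0.447 (t) or 0.17/1.96 × √29 = 0.467 (normal). These bracket 0.46.
- As an interval for an SD of 0.46 on 28 df it would be (0.37, 0.62), with a ratio of limits of 1.70. The quoted ratio is 0.72/0.38 = 1.89. This reading does not fit.

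The mean-difference reading is therefore the one consistent with 0.46. It also suggests that 0.46 is an SD of differences, which would make the stated 80% conservative for detecting 0.35. I carry both readings.

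**3. Non-inferiority power if 0.35 were the margin.** Power = P(T > t(0.975, 28)), with noncentrality (0.35 − true difference)/(SD of differences/√30).

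| True difference (mEq/L) | SD of differences 0.651 | SD of differences 0.46 |
|---|---|---|
| 0 | 81% | 98% |
| 0.1 | 53% | 82% |
| 0.2 | 23% | 41% |
| 0.38 (lower limit of the cited interval) | 1.4% | 1.1% |
| 0.55 (its midpoint) | 0.02% | 0.001% |

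With one-sided 0.05, the power at 0.55 is 0.04% and 0.003% (normal approximation).

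**4. Dependence on the margin.** When the margin equals the true difference, power equals the one-sided error rate. At a true difference of 0.55, any margin up to 0.55 therefore gives at most 2.5%. For 80% power at 0.55 the margin would have to be about 0.55 + 2.80 × SD/√30, which is 0.79 with an SD of 0.46 and 0.88 with 0.651. Both are more than twice 0.35.

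**The case against.** The power statement agrees with most of the document. The superiority label, the wording about detecting a difference and the paired comparison at p below 0.05 all describe a test of difference, and for that test the 80% is right. At a true difference of 0.55 such a test would have 99.4% power or more. Only Objectives departs from this. That stands, and it is why one remedy is simply to reword Objectives. It does not remove the point, because Objectives states the primary hypothesis.

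The 0.35 is called a minimal clinically important difference and is never declared a margin. That also stands. The table is conditional on it, although the result at 0.55 holds for any margin up to 0.55. The full protocol or analysis plan may contain a margin, but the mismatch between the hypothesis and the power figure is in the article itself.

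A reader might infer that the plan's own evidence refutes its hypothesis, or that the trial has essentially no power. The document does not support this. The plan takes only the spread from the cited study; its effect size comes from a different trial. The source's potassium contrast, potassium source and direction are not described beyond its being called similar. Background and rationale also gives a qualitative reason to expect a smaller rise from fruit and vegetables: their carbohydrate promotes insulin secretion and potassium uptake into cells, and they supply bicarbonate. What remains is that Sample size neither uses nor quantifies that argument.

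Finally, the abstract presents the findings as evidence for or against restriction, so a result that goes against the hypothesis would still be informative. I agree; the issue is what the power figure describes.

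**Conclusion.** The point holds in conditional form. The primary hypothesis is non-inferiority, while the sample size, the design label and the analysis are those of a test of difference. The stated 80% carries over to non-inferiority only if 0.35 is the margin and the true difference is zero. Under the SD reading that reproduces the 80%, true differences of 0.1 and 0.2 bring the power down to 53% and 23%; under the other reading they give 82% and 41%.

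The figure of below 0.1% at 0.55 rests on three assumptions that the document does not state: that the cited interval is a mean difference, that it is higher-potassium minus lower-potassium, and that 0.35 (or at least no much larger value) is the margin. It shows that the plan should address the interval's location. It does not predict that the trial will fail.

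**What to change.** Reconcile Objectives, Trial design and Sample size in one of two ways.

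1. Make the test of difference primary, reported with its estimate and 95% confidence interval, and reword the hypothesis in Objectives to match. The stated 80% then applies as it is.
2. Keep non-inferiority and correct the label in Trial design. In Sample size, state the margin and the assumed true difference, replace the 80% with the non-inferiority power at true differences of 0, 0.1 and 0.2, and add one sentence explaining why the 0.55 midpoint of the cited study is not expected here. The argument in Background and rationale could serve if it is tied to a number.

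Under either option, say what the interval (0.38, 0.72) estimates and whether 0.46 is a within-subject SD or an SD of differences.

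The cost is protocol wording and, under the second option, probably a less favourable stated power. Neither option changes the number of patients or the data collected.

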### Recruitment

The recruitment for this study will be done by the research coordinator who will work directly with a healthcare professional (such as a nurse or physician) within the participants circle of care. The healthcare professional will help identify potentially eligible participants. If the participant consents to be contacted, the research coordinator will meet the participant through a virtual meeting or an in-person visit to collect informed consent to participate in the study. A total of thirty participants will be recruited to participate in this study, from Seven Oaks Hospital and Health Sciences Centre renal clinics in Winnipeg, Manitoba. The recruitment period is targeted to last thirty weeks, with enrolment predicted to go at a rate of one participant per week.

